#### Publication policy

Trial results will be published in a medical journal and released to the participating physicians, patients, and general medical community. Full trial protocol, full study report, anonymized results of the trial, and statistical data set will be provided on demand to the medical community.

### Duration of study and sample size calculation

Due to insufficient and reliable data regarding suitable endpoints for the treatment of anastomotic leaks, a sample size calculation is not possible at this point. The aim of this study is, among other things, to evaluate the feasibility of a RCT and to collect data in order to enable adequate sample size calculation for future larger interventional trials. Based on the rate of leakage and an estimated inclusion rate of 80% of the patients, the duration of the study is calculated to be 48 months with a 24-month recruitment phase (Fig. 3).

**Fig. 3 Fig3:**
[figure not shown]
Timeline and important milestones of the study

#### Trial management and monitoring

Trial management is conducted by the principal investigator and research physicians of each participating study center who are part of the trial management committee. Standardized monitoring of 20% of the data and essential material is conducted by an external clinical research organization. Both therapeutic regimens applied in this are clinically well-established and investigated therapies and there will be no blinding. Therefore, no study-specific harm was identified and the study was classified as low-risk. As a consequence, no DMC is planned.

### Statistical analysis

The primary analysis and the analysis of the secondary endpoints will be conducted according to the intention-to-treat (ITT) principle including all patients. Each patient will be analyzed independent of the group allocation.

To assess the quality of life, either a t-test for independent groups or a Mann-Whitney U test is performed at the two-sided level of 5% depending on the distribution type.

For statistical evaluation of the secondary endpoints, parametric and non-parametric analyses will be conducted depending on the distribution type.

*p*-values < 0.05 are considered statistically relevant, but merely in a descriptive manner. Quantitative variables are described by mean value, standard deviation, and quartiles, and qualitative variables by absolute and relative frequency. The effect size is calculated as follows: With two unrelated samples (*n* = 20), α = 0.05, and power = 0.8, an effect of 0.909 can be calculated.

All comparisons with respect to the targets explicitly mentioned elsewhere are exploratory and therefore differences are considered significant if the respective p-value is less than 0.05. Subgroup analyses regarding, e.g., SOFA scores are planned.

The analysis of the data will be performed as an intention-to-treat analysis. In case of missing data, the effect on the results will be assessed via sensitivity analysis of augmented data sets. Reasons for missing data will be analyzed and qualitatively compared between the two groups.

In advance, all planned analyses will be specified in a statistical analysis plan (SAP), which will be finalized based on pooled data analysis before the first comparative analysis. No interim analysis is planned for this trial.

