### Patients

This study will be conducted at the University Hospital of Cologne and the University Medical Center Hamburg-Eppendorf and include a total of 40 patients (n=40). The number of patients is estimated in order to show the feasibility of the trial protocol and to provide data to calculate the sample size for a larger randomized prospective interventional trial.

All patients with resectable esophageal cancer will be screened for eligibility to be enrolled in the study. Informed consent will be obtained preoperatively before the inclusion criterion of an anastomotic leak is satisfied.

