### Randomization

In case of clinical, radiological, or laboratory suspicion of an anastomotic leak after Ivor Lewis esophagectomy, a diagnostic upper gastrointestinal endoscopy will be performed. If an anastomotic leak is verified endoscopically and all inclusion and exclusion criteria are met, patients will be randomly assigned to either control (SEMS) or experimental (EVT) group with a 1:1 allocation using a web-based, centralized permuted block randomization system. The allocation will be final and the researchers will not be able to influence the results. Due to the character of the intervention, a blinding is impossible.

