### Effect evaluation

#### Primary effect measure

The primary endpoint of this study is the subjective quality of life assessed by the patient using a systematic and validated questionnaire from the European Organisation for the Research and Treatment of Cancer (EORTC QLQ C30, EORTC QLQ-OES18 questionnaire), which incorporates nine multi-item scales: five functional scales (physical, role, cognitive, emotional, and social), three symptom scales (fatigue, pain, and nausea and vomiting), and a global health and quality-of-life scale [23–25]. The evaluation will be performed at screening, after randomization before treatment, day 7 (±2) after randomization, upon discharge from the hospital, and 1 (±5 days), 3, and 6 months after randomization (±14 days). After inclusion, data will be transferred to the CRF.

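### The stated primary quality-of-life comparison has no baseline term and does not fix what is estimated; adjusting for the screening score would gain precision at small cost

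*Protocol article*

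**What the plan says.** The Statistical analysis section gives one method for the primary endpoint: "either a t-test for independent groups or a Mann-Whitney U test is performed at the two-sided level of 5% depending on the distribution type". It names no covariate and no criterion for judging the distribution. The same section gives the detectable effect for two unrelated samples of 20: "α = 0.05, and power = 0.8, an effect of 0.909 can be calculated". It also calls p-values descriptive and defers all planned analyses to a SAP that is to be finalized on pooled data before the arms are compared.

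The Primary effect measure section lists the assessments: "The evaluation will be performed at screening, after randomization before treatment, day 7 (±2) after randomization, upon discharge from the hospital", followed by 1, 3 and 6 months. It describes nine multi-item scales. Table 1, in the Follow-up section, also marks the questionnaire at screening but has no mark for it in the column for the time before treatment. Under Patients, consent is preoperative. The design is open, and the Randomization section says that blinding is impossible.

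**The concern.** Two features of the stated analysis look weak for a trial of 40 patients.

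First, a pre-randomization score on the same scale is collected from every consenting patient but has no place in the analysis. With 20 per arm, chance differences at baseline are common. An unadjusted test neither corrects for them nor removes the outcome variance that the baseline explains.

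Second, the t-test concerns a mean difference and the Mann-Whitney test concerns rank ordering. If the distribution decides between them, the quantity reported can differ between scales and visits. The section's nine scales and five post-treatment times (day 7, discharge, 1, 3 and 6 months) give 9 × 5 = 45 comparisons, each open to either test.

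This matters more because the trial's stated purpose is to supply figures for sizing a later one. A Mann-Whitney p-value supplies neither a mean difference nor an SD. An adjusted difference, a residual SD and a baseline-outcome correlation are direct planning inputs.

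**Working it through.** **Inputs from the article.** 40 patients allocated 1:1, so n = 20 per arm; two-sided α = 0.05; power 0.80; stated detectable effect 0.909 SD. **Assumed:** the correlation r between screening and follow-up scores, which the article does not give. It is varied from 0 to 0.7.

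**1. The plan's own figure.** For an unadjusted two-sample t-test the noncentrality is d × √(n/2) = d × √10, with 38 degrees of freedom. Solving for 80% power gives d = 0.9091, and power at 0.909 is 79.99%. The stated figure reproduces as that of an unadjusted test.

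**2. Chance imbalance at baseline.** The standard error of the baseline difference is √(2/20) = 0.316 SD. By the normal distribution, an imbalance above 0.3 SD in either direction occurs in about 34% of such trials, and above 0.5 SD in about 11%.

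**3. ANCOVA on the screening score.** The residual SD is SD × √(1 − r²), with 37 degrees of freedom. At r = 0 the detectable effect is 0.910, so in general it is 0.910 × √(1 − r²). For example, at r = 0.5 it is 0.910 × 0.866 = 0.788. Expected chance imbalance multiplies the variance by 1 + 1/(2n − 4) = 1 + 1/36, that is, the detectable effect by 1.014.

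| r | Detectable effect (SD) | With imbalance | Power at 0.909 | With imbalance |
|---|---|---|---|---|
| 0 | 0.910 | 0.922 | 79.9% | 78.8% |
| 0.2 | 0.891 | 0.904 | 81.5% | 80.5% |
| 0.3 | 0.868 | 0.880 | 83.5% | 82.5% |
| 0.5 | 0.788 | 0.799 | 89.8% | 89.0% |
| 0.7 | 0.650 | 0.659 | 97.5% | 97.2% |

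With imbalance included, the break-even is r ≈ 0.17. The worst loss is at r = 0: 80.0 − 78.8 = 1.2 power points.

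**4. Incomplete pairs.** At r = 0.5, imbalance included, ANCOVA power is 80.5% with 16 complete pairs per arm and 77.6% with 15. Compared with an unadjusted test on all 20, the gain is gone at about 15.

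**5. Change scores.** A t-test on change from screening has SD × √(2(1 − r)). Its detectable effect is 1.076, 0.909 and 0.704 SD at r = 0.3, 0.5 and 0.7. It is worse than ANCOVA at each of these values, and worse than ignoring the baseline when r is below 0.5.

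**6. The choice of test.** The article gives no rule, so one was assumed: Shapiro-Wilk at 0.05 in each arm, then the t-test if both pass and Mann-Whitney otherwise. With 8,000 simulated trials of 20 per arm, type I error was 5.0% (normal data), 5.5% (13-level scale), 5.2% (skewed scale) and 5.0% (exponential). The simulation error is √(0.05 × 0.95/8,000) = 0.24 points, and on the 13-level scale the t-test alone also gave 5.5%. The two tests gave different verdicts in about 2–4% of data sets without an effect and 4–14% with one. When the means were equal but the shapes differed (exponential against normal), rejection was 5.7% for the t-test and 7.3% for Mann-Whitney, as expected of tests with different targets.

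**7. Which baseline.** The Primary effect measure section and Table 1 agree only on the screening score, which precedes randomization. The assessment described in "The evaluation will be performed at screening, after randomization before treatment" is absent from Table 1. In an open trial, a patient may also know the allocation when completing it.

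**The case against.** The strongest reply is that covariates and a distribution rule are ordinary SAP content, and that a SAP is promised before any comparison. This stands in part. A reader might infer that the test could be picked after seeing which one favours a treatment, but fixing the SAP on pooled data before comparison argues against that. The deferral does not undo the rule that the protocol itself states, and a SAP that follows the protocol would inherit it. Pooled data also mix the arms, so a treatment effect can itself distort the distribution being judged.

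Second, the sentence does not say that raw follow-up scores are compared; a test on change from screening would fit it. That is possible, but the quoted 0.909 is given for two unrelated samples without adjustment, and change scores are the less precise use of the baseline (step 5).

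Third, this is a pilot with descriptive p-values, declared too small to settle superiority, so added power changes no decision. That is fair, and it limits the severity. It also makes estimation the main product, which favours a fixed, adjusted estimate.

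Fourth, the screening score precedes both the esophagectomy and the leak, so its correlation with later scores may be low. This stands. A reader might infer that adjustment is free or always better; the documents give no correlation from which to say so.

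**Conclusion.** The point holds as a worthwhile, inexpensive improvement to a method that the protocol states, not as an error that invalidates the trial. With 20 complete pairs per arm, adjustment moves the detectable effect from 0.909 SD to about 0.87–0.88, 0.79–0.80 or 0.65–0.66 SD at assumed correlations of 0.3, 0.5 or 0.7. The cost is one degree of freedom and about one power point at worst if the correlation is below about 0.17. These figures assume a linear relation with a common slope and few missing screening scores.

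The harm of the distribution-dependent test is an unfixed quantity of interest. A reader might infer an inflated false-positive rate, but simulation under an assumed selection rule gave 5.0–5.5%, which does not support that. Nor does the questionnaire taken after randomization undermine the proposed analysis, which relies on the screening score. That assessment is merely unsuitable as a covariate, and its place in the schedule is inconsistent. A reader might also expect a centre term, but the Randomization section describes permuted blocks without saying that they are stratified by centre, so the text gives no basis for requiring one.

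**What to change.** In the protocol and SAP, before any comparative analysis:

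- Name one quality-of-life scale and one time point as primary; ANCOVA cannot be run as a primary analysis without them.
- Specify ANCOVA of that follow-up score on treatment, adjusted for the screening score of the same scale. Report the adjusted mean difference with 95% CI, the residual SD and the baseline-outcome correlation.
- Keep Mann-Whitney as a sensitivity analysis and delete the distribution-dependent choice for the primary endpoint.
- State how missing screening scores are handled, so that patients are not dropped for lacking one.
- Do not use the questionnaire taken after randomization as the covariate. Reconcile the Primary effect measure section with Table 1 on whether that assessment takes place.

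The cost is wording and one degree of freedom. No additional patients, visits or questionnaires are needed.

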## Discussion

Anastomotic leaks after esophagectomy remain a major postoperative complication, representing a potentially life-threatening condition for the patient. Thus, new therapeutic approaches need to be well established and compared to the current standard to achieve the best possible outcome. Up to date, there has been more of an eminence-based rather than an evidence-based therapeutic approach to anastomotic leaks justified by the proclamation of the importance of individualized treatment strategies. Treatment of anastomotic leaks is already difficult and complicated by the lack of defined criteria such as the size of the leak or the existence of a wound cavity for the choice of the best endoscopic treatment strategy. So far, this calls for an individualized treatment regime, which is chosen depending on the expertise and equipment of the treating clinic. In our opinion, this is not the optimal basis for such an important and consequential therapeutic decision, so that the long-term goal should at least be the attempt to establish a standardized treatment. With our study, we would like to lay a first foundation to possibly be able to answer the question in the future, whether a standardized protocol can be established for such a complex clinical situation as an anastomotic leak. This also implies taking into account some possible protocol deviations.

Current evidence is not conclusive enough to make clear recommendations as well as to define variables that favor one treatment strategy over the other. The latest meta-analysis comparing implantation of SEMS with EVT suggested a higher success rate for EVT and thus calling for further prospective interventional trials [21]. However, the underlying retrospective trials do not permit a final recommendation due to significant bias and methological weaknesses. Prospective data regarding this important question are missing.

The ESOLEAK trial is the first prospective study comparing both treatments in the presence of esophageal anastomotic leaks. Due to the exploratory design of this pilot study, obviously, the sample size is too small to answer the question, whether EVT or SEMS implantation represents the superior treatment strategy. The aim of the trial is to evaluate the feasibility of planned RCTs and to find suitable endpoints for the treatment of anastomotic leaks as well as to enable an adequate sample size calculation for future interventional trials. It is very difficult to select an endpoint that does equal justice to both therapeutic approaches taking into account their different ways of application: continuous therapy with few endoscopies (SEMS) vs. frequent endoscopic change and control (EVT). By selecting the quality of life as a primary endpoint, we chose a soft, but from our perspective very important and often underrepresented parameter that is appropriate to analyze patients in both treatment arms in a standardized manner.

In summary, the two main endoscopic strategies for contained leaks after Ivor Lewis esophagectomy—SEMS and EVT—are compared in a prospective, randomized fashion for the first time. The results of the ESOLEAK study are intended to lay the foundation for larger interventional trials tackling this issue and to contribute essential evidence to the treatment of this severe complication.

## Trial status

Study protocol version 1.1, 23.05.2019

Estimated study start date: 1 December 2020

Approximate date when recruitment will be completed: 1 December 2022

Not yet recruiting

## Data Availability

The data of the current study is not planned to be used in further trials.

## Abbreviations

ASA score: American Society of Anesthesiologists score
CE certified: Conformité Européenne
CRF: Case report form
CRP: C-reactive protein
ECG: Electrocardiography
EORTC QLQ: European Organization for Research and Treatment of Cancer Quality of Life Questionnaire
EVT: Endoscopic vacuum therapy
ITT: Intention-to-treat
ml: Milliliters
mmHg: Millimeters of mercury
SAE: Serious adverse event
SAP: Statistical analysis plan
SEMS: Self-expanding metal stents
SOFA score: Sequential Organ Failure Assessment score
RCT: Randomized controlled trial
RECIST: Response Evaluation Criteria in Solid Tumors
TNM: Classification of Malignant Tumors
